### Statistical considerations

#### Sample size estimation

The possible mode of action of empagliflozin on endothelial function remains to be determined due to the current lack of available evidence. In the EMPA-REG OUTCOME trial, empagliflozin did not affect the incidence of major atherosclerotic macrovascular events such as myocardial infarction and stroke [10], providing results that were comparable to the CV safety trials investigating dipeptidyl peptidase-4 (DPP-4) inhibitors. Empagliflozin markedly reduced the predefined composite CV outcome and hospitalizations for heart failure, whereas the trials assessing DPP-4 inhibitors did not demonstrate such reductions [38–40]. Given these background results, we hypothesized that the putative pharmacological effects of empagliflozin on endothelial function would at least be equivalent to the effect of DPP-4 inhibitors. Therefore, the sample size in the present trial was calculated on the basis of detecting similar treatment effects on endothelial function via assessments of the RHI. Hashikata et al. [32] reported that 3 months of treatment with teneligliptin, a DPP-4 inhibitor, improved the mean (±standard deviation [SD]) RHI from 1.58 ± 0.47 to 2.01 ± 0.72 in patients with T2DM. Therefore, we expected the mean changes in the RHI from baseline would be 0.40 in the empagliflozin group and 0.06 in the placebo group after 24 weeks of treatment with an estimated the difference between groups of 0.34 ± 0.06. At an alpha level of 5% for a two-sided test, a sample size of 50 patients per arm was needed to provide a power of 80% for each comparison. Taking into consideration the possibility of an estimated 10% dropout rate, we estimated that 55 patients per arm (N = 110 patients) will be the appropriate sample size to provide sufficient statistical power for this trial.

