### Randomization and blinding

Eligible and consenting participants will be randomized (1:1), in a double-blind manner to either receive empagliflozin (10 mg once daily) or a placebo treatment (once daily), using the web-based minimization dynamic allocation method balancing for HbA1c (<7.0 or ≥7.0%), age (<65 or ≥65 years), systolic blood pressure (BP) (<140 or ≥140 mmHg), and current smoking status (nonsmoker or smoker) at the time of screening [33, 34].

After randomization, patients, investigators, the sponsors, and other individuals involved with various aspects of the trial (e.g., including the conduct or data analysis) are to remain masked to group assignments until after the database is locked and prior to the statistical analysis. Only a predesignated study person will have access to the sealed randomization key codes that will allow unblinding under circumstances considered an emergency and when the identity of the trial drug must be revealed strictly to the investigator for the purpose of providing appropriate medical treatment due to serious adverse effects or ensuring the safety of a trial participant. If the key code for any patient is opened, the principal investigator must be informed immediately of the unblinding incident.

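### The planned difference of 0.34 with ±0.06 does not give 50 patients per arm at 80% power under any standard reading of the ±; a common SD of about 0.60 would

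*Protocol article*

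**What the plan says.** All the inputs stand in one paragraph of the protocol article, under Sample size estimation. It starts from a study of teneligliptin that "improved the mean (±standard deviation [SD]) RHI from 1.58 ± 0.47 to 2.01 ± 0.72 in patients with T2DM". From this the authors expect mean changes that "would be 0.40 in the empagliflozin group and 0.06 in the placebo group after 24 weeks of treatment", and they summarise the contrast as "the difference between groups of 0.34 ± 0.06". The test is set out as "At an alpha level of 5% for a two-sided test", and the result is that "a sample size of 50 patients per arm was needed to provide a power of 80% for each comparison". An allowance of 10% for dropout raises this to 55 per arm, 110 in total. Allocation is 1:1 (Randomization and blinding).

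The ±0.06 is the only measure of spread attached to the planned effect, and it carries no label. One sentence earlier, the ± on the cited RHI values is labelled as an SD. No SD of the change in RHI is given anywhere else in the article.

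**The concern.** For a comparison of two means, the sample size follows from the difference, the SD, alpha and power. Three of these are stated clearly, so the fourth can be checked against the stated 50 per arm. Whatever 0.06 is taken to be, it is far too small to require 50 per arm.

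The SD of the change is the one nuisance parameter behind the size of the trial, and the change in RHI is the primary endpoint. When the results are read, above all if they are null, a reader will compare the observed SD with the planned one to judge whether the trial had the power it claimed. Against a printed 0.06 that comparison tells the reader nothing.

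**Working it through.** **Inputs** (protocol article, Sample size estimation; allocation from Randomization and blinding): difference d = 0.40 − 0.06 = 0.34; two-sided alpha 0.05; power 0.80; 1:1; 50 per arm; spread ±0.06, unlabelled.

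**Formula.** Normal approximation: n per arm = 2 × [(1.96 + 0.8416) × SD / d]². The exact figures below use the noncentral t distribution for the two-sample t test. At 50 per arm the standard error of the difference is SD × √(2/50) = 0.2 × SD.

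**Attempt to reproduce 50 per arm from ±0.06**

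| Meaning given to 0.06 | Implied SD | n per arm, normal formula before rounding up | n per arm, t test | Power at 50 per arm, t test |
|---|---|---|---|---|
| SD | 0.06 | 0.49 | 2 | about 100% |
| Variance | √0.06 = 0.245 | 8.1 | 10 | above 99.99% |
| SE of the difference at 50 per arm | 0.06 / 0.2 = 0.30 | 12.2 | 14 | 99.99% |
| SE of each arm's mean at 50 per arm | 0.06 × √50 = 0.42 | 24.4 | 26 | 97.8% |
| Half-width of the 95% CI of the difference | 0.06 / 1.96 / 0.2 = 0.153 | 3.2 | 5 | about 100% |

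None comes near 50. On the SD reading, a one-sided alpha, 90% power, or a difference of 0.28 or 0.40 still gives 1 per arm by the normal formula.

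**Solving backwards from 50 per arm at 80% power**

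- Normal approximation: SD = 0.34 / (2.8016 × 0.2) = 0.607.
- t test: SD = 0.601.
- Forward check with SD 0.60: the normal formula gives 48.9, so 49; the t test gives 50, with 80.1% power.
- Corresponding SE of the difference: 0.2 × 0.60 = 0.12.

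**Size of the discrepancy.** SD reading: 0.60 / 0.06 = 10. SE-of-the-difference reading: 0.12 / 0.06 = 2.

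**Is 0.60 compatible with the cited SDs, 0.47 and 0.72?** Yes, by more than one route:

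- Simple mean: (0.47 + 0.72) / 2 = 0.595. The t test gives 50 per arm, power 80.8%.
- Root mean square: √[(0.47² + 0.72²) / 2] = 0.608. The normal formula gives 50.2, so 51; the t test gives 52.
- SD of a within-patient change: √(0.47² + 0.72² − 2r × 0.47 × 0.72) equals 0.60 when r = (0.2209 + 0.5184 − 0.36) / 0.6768 = 0.56.

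The article does not say which of these, if any, was used.

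**Dropout.** 50 × 1.1 = 55, as stated. Dividing by 0.9 gives 55.6, so 56. That difference of one patient is immaterial.

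**The case against.** The strongest reply is that this is a reporting slip and the design is sound. The ± is unlabelled on the planned difference, where a standard error would also be natural. An SD of 0.06 is also impossible beside the cited values: with SDs of 0.47 and 0.72, the SD of a change cannot fall below 0.72 − 0.47 = 0.25 even at perfect correlation. A careful reader would see a misprint, and the cited SDs lead to about 50 per arm anyway.

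Much of this stands, and it limits what may be inferred:

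- A reader might conclude that the figure is wrong by exactly a factor of ten. That holds only if ± means SD. A misplaced decimal point would explain it, but 0.06 is also the expected placebo change, so a copying slip is equally possible.
- A reader might conclude that the trial is many times too large, or that it is underpowered. The documents support neither. The first takes the misprint at face value; the second needs an SD above 0.60, for which there is no evidence.
- A reader might take a correlation of 0.56 to be the hidden planning assumption. It is back-solved, and the simple mean of the cited SDs gives 50 per arm without any correlation.
- Power figures built on change-score SDs at assumed correlations would not describe the planned analysis, which estimates baseline-adjusted means by analysis of covariance (Statistical analysis plan section).

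Two defences fail. That an article condenses the full protocol excuses omissions, but this is a printed figure that conflicts with the sentence after it. Covariate adjustment does not help either: it lowers the required n, so it cannot raise 2, 14 or 26 to 50.

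**Conclusion.** The point holds as an error in a stated planning figure. With a difference of 0.34, two-sided 5% and 80% power, ±0.06 leads to between 2 and 26 patients per arm, depending on its meaning, and never to 50. A common SD of about 0.60 gives 50. The discrepancy is about tenfold on the SD reading, which matches the labelling in the preceding sentence, and about twofold if the SE of the difference was meant.

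This rests on an unadjusted two-sample t test with equal SDs and 1:1 allocation; the article does not name the test behind its calculation. That 0.60 was the SD actually used is an inference from the result. The finding concerns the justification of N. It leaves the test, alpha and N as they are, and it does not show that 50 per arm is inadequate.

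**What to change.** Go back to the original calculation and replace the ±0.06 with the SD of the change in RHI that was used, labelled as an SD and with its source, including how it was obtained from the cited 0.47 and 0.72 if it was. If 50 per arm and 80% power are both correct, that SD will be about 0.60. If the calculation used something else, restate the power that 50 per arm provides under it. The cost is one look at the calculation file and one corrected sentence, carried into the statistical analysis plan if the figure is repeated there. N stays at 110.

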#### Statistical analysis plan

The analyses of the primary and secondary endpoints will be performed in the full analysis set, which includes all participants who received at least one dose of treatment during the trial period and who did not have any serious violation of the trial protocol, such as not providing informed consent or registration outside of the trial period.

Summary statistics will be used to calculate the baseline characteristics including the frequencies and proportions for categorical variables and mean ± SD for continuous variables. The patient characteristics will be compared using Chi square tests for categorical variables, t tests will be used for normally distributed continuous variables, and the Wilcoxon rank sum tests will be employed for continuous variables with a skewed distribution.

For the primary analysis—a comparison of treatment effects between the treatment groups—the baseline-adjusted means and their 95% confidence intervals will be estimated by analysis of covariance adjusted for the following allocation factors at the time of screening: HbA1c (<7.0 or ≥7.0%), age (<65 or ≥65 years), systolic BP (<140 or ≥140 mmHg), and current smoking status (nonsmoker or smoker). The primary analysis will not take missing observations into account and the mixed effects model for repeated measures (MMRM) will be used as a sensitivity analysis to examine the effect of missing data. In addition, MMRM will also be used as a sensitivity analysis to assess changes in the RHI during the trial period and be modelled as a function of time and treatment, and the treatment-by-time interaction will be evaluated. Subgroups for the analyses will be defined based on, but not limited to, the RHI at baseline (e.g., <2.0 or <1.67). A secondary analysis will be performed in the same manner as the primary analysis. In addition, correlations between the changes in the RHI and each measurement listed as a secondary endpoint will be evaluated using Pearson’s correlation coefficient.

The principal investigator and a biostatistician will develop the statistical analysis plan before completion of patient recruitment and database lock. All p values will be two-sided, and p values <0.05 will be considered statistically significant. All statistical analyses will be performed using SAS software version 9.4 (SAS Institute, Cary, NC, USA).

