### Trial design and follow up

All consenting and eligible participants are randomized to receive either empagliflozin or a placebo treatment. Post-randomization follow-up visits are scheduled at 4, 12, and 24 weeks (Fig. 1). Each participant will see their usual-care physician at each visit to receive usual-care and individualized treatment according to their background disease, in addition to administration of the study drug.

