### Measurements

The baseline characteristics of all patients, including gender, age, body height, body weight (BW), duration of T2DM, complications, background treatment, and smoking and drinking habits are to be recorded prior to randomization. Each participant’s background treatment and trial medication will be recorded at each visit. BP, heart rate (HR), and BW will be measured at baseline and at each visit. The following assessments and methodology will be employed at baseline and at 24 weeks: peripheral endothelial function will be assessed using the RH-PAT test (details described later), the R–R interval coefficient of variation will be determined using electrocardiograms, left ventricular ejection fraction (LVEF) using the modified Simpson method and E/e’ using the tissue Doppler imaging will be measured by echocardiograms, brachial–ankle pulse-wave velocity (baPWV) will be measured using a volume-plethysmographic apparatus as previously described [37]. These physiological tests are to be evaluated locally by technicians at each site. Blood tests will also be performed at baseline and 24 weeks (details listed in Additional file 1), as will specific biomarker assays for N-terminal pro-brain natriuretic peptide (NT-proBNP), interleukin-8 (IL-8), high-sensitivity troponin-I (hs-TnI), receptors for advanced glycation end products (RAGE), and angiopoietin-like protein 2 (ANGPTL2). Biomarkers will be measured at central laboratories. Urinary ketone bodies are to be evaluated qualitatively at each visit. Creatinine-corrected urinary albumin excretion and urinary liver-type fatty acid-binding protein (L-FABP) will be measured at baseline and 24 weeks. In addition, participants will be examined at each visit for symptomatic genital or urinary infections that need to be treated with antibiotics.

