#### Measurement of RH-PAT

Peripheral endothelial function will be evaluated by performing RH-PAT using the Endo-PAT2000 device (Itamar Medical, Caesarea, Israel). The principles and measuring procedures of RH-PAT have been described in detail elsewhere [25, 26, 31]. In brief, measurements are performed in the morning at baseline and at 24 weeks, in a quiet, light- and temperature-controlled room, and when the examinee is in a fasted state and in a stable condition before taking their medication for the day. A BP cuff is placed on the upper arm and the opposite arm serves as a control. PAT probes are put on one finger of each hand. After at least a 15-min resting period on a bed in the supine position, the patient’s baseline pulse amplitude is recorded from each fingertip for 6 min. The cuff is subsequently inflated to 60 mmHg above systolic BP or 200 mmHg for 5 min. Finally, the pulse amplitude after cuff deflation is recorded for 5 min. The RHI is automatically calculated by a computerized algorithm in an operator-independent manner [25, 31]. At the same time, the augmentation index (AI) and heart rate variability (HRV), including the standard deviation of the normal to normal intervals (SDNN) and the ratio of low-to high-frequency (LF/HF) are also calculated automatically by using the Endo-PAT2000 software (above version 3.4.4).

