### Trial endpoints

The primary endpoint in this trial is the change in RHI from baseline to 24 weeks. Secondary endpoints are baseline to 24 week changes in the following parameters and their correlation with the RHI: double product, calculated as heart rate × systolic BP; baPWV; coefficient of variation of the R–R intervals (including the differences between the results at rest and those during deep breathing) and the standard deviation of heartbeat intervals; LVEF and E/e’; specific biomarkers, including NT-proBNP, IL-8, hs-TnI, RAGEs, and ANGPTL2; renal function, including serum creatinine, eGFR, and creatinine-corrected urinary albumin excretion and L-FABP; glycemic parameters, including HbA1c, fasting blood glucose, and glycoalbumin; clinical parameters, including BP, pulse pressure (systolic BP minus diastolic BP), HR, BW, body mass index, and laboratory measures (details listed in Additional file 1); AI, SDNN, and LF:HF evaluated by the Endo-PAT2000.

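### With RHI measured only once after baseline, the planned MMRM says little about the effect of missing week-24 data

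*Protocol article*

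**What the plan says.** Under Trial endpoints, "The primary endpoint in this trial is the change in RHI from baseline to 24 weeks". The Statistical analysis plan section analyses it by ANCOVA, reports baseline-adjusted means, and names four allocation factors as covariates (HbA1c, age, systolic BP, smoking). The primary analysis makes no allowance for missing observations.

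The same section then gives MMRM two tasks. First, "the mixed effects model for repeated measures (MMRM) will be used as a sensitivity analysis to examine the effect of missing data". Second, it is to describe RHI over the course of the trial as a function of time and treatment, where "the treatment-by-time interaction will be evaluated". The article names no other missing-data analysis.

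On the schedule, Trial design and follow up states: "Post-randomization follow-up visits are scheduled at 4, 12, and 24 weeks". RH-PAT is not done at all of these visits. Measurements says: "The following assessments and methodology will be employed at baseline and at 24 weeks: peripheral endothelial function will be assessed using the RH-PAT test". Measurement of RH-PAT agrees: "measurements are performed in the morning at baseline and at 24 weeks". By contrast, "BP, heart rate (HR), and BW will be measured at baseline and at each visit".

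**The concern.** An MMRM helps with dropout when patients who leave early have already given intermediate values of the outcome. Those values, with the within-patient correlation, inform the final visit. RHI has no intermediate values. A patient who lacks week 24 contributes at most a baseline measurement, which the completers' ANCOVA already conditions on if it adjusts for baseline RHI.

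What is at stake is how the check will be read. If the MMRM agrees with the ANCOVA, the report may claim robustness to missing data although nothing has been varied. If it disagrees, the gap may be put down to missing data although it has another source.

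The article gives some reason to care. It allows for 10% dropout. Its discontinuation criteria (Table 2) include poor glycaemic control, dehydration and adverse drug effects, which could differ between arms. The Discussion says that intravascular volume affects RH-PAT and that this drug class can deplete volume. None of this shows that missingness will depend on the unobserved RHI, but it makes a real check worthwhile.

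**Working it through.** The article gives no figure for the MMRM, so there is none to reproduce. The planned difference is 0.40 − 0.06 = 0.34.

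**Inputs from the article:** 110 patients, 1:1; expected changes 0.40 and 0.06; 10% dropout; baseline SD 0.47 (from the DPP-4 inhibitor study cited under Sample size estimation). **Assumptions:** baseline mean 1.6, slope of week 24 on baseline 0.5, residual SD 0.5, missingness depending on baseline RHI. The four allocation factors were left out of the simulation.

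**Algebra.** Let Y0 be baseline RHI and Y1 week-24 RHI. The joint density factors as f(Y0) × f(Y1 | Y0). A dropout contributes only f(Y0). Write E(Y1 | Y0, arm) = a + τ·arm + β·Y0. Then τ and β are estimated from completers alone, and τ is the ANCOVA treatment effect. (The arm coefficient is the same for Y1 or for Y1 − Y0 once Y0 is a covariate.)

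1. *Baseline as covariate, week 24 the only response.* Dropouts supply no response, so the model is the completers' ANCOVA and the difference is exactly 0. With one time point, a treatment-by-time term cannot be estimated.
2. *Baseline as a response, common mean in both arms.* The treatment difference in change is τ, again the ANCOVA estimate.
3. *Baseline as a response, separate arm means (time, treatment and interaction).* The interaction is τ + (β − 1)·d, where d is the baseline difference between arms in all patients. It departs from ANCOVA by (β − 1)·d.

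**Numerical check**, 20 simulated trials with on average 12 of 110 week-24 values missing:

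| Form | Difference from completers' ANCOVA | Mean SE (ANCOVA 0.100) |
|---|---|---|
| 2, common mean | at most 0.00000002 | 0.099 |
| 3, separate means | mean 0.035, maximum 0.084 | 0.108 |

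The form 3 estimates matched the formula to 0.000000005. The trial with the largest gap shows the mechanism: ANCOVA 0.5328, form 3 0.4491, baseline difference 0.151. The gap is 0.4491 − 0.5328 = −0.0837, so the implied β − 1 is −0.0837 / 0.151 = −0.55, near the assumed 0.5 − 1 = −0.5. Relative to the planned effect, 0.035 / 0.34 = 10% and 0.084 / 0.34 = 25%. These gaps come from chance baseline imbalance, not from recovered week-24 data.

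**Unobserved values.** In none of the three forms does the estimate depend on what the missing week-24 values would have been. For scale only, with 10% of one arm missing and an assumed shift in those patients:

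- 0.10 × 0.34 = 0.034, and 0.034 / 0.34 = 10%
- 0.10 × 0.60 = 0.060, and 0.060 / 0.34 = 18%

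Both shifts are assumptions. The lower equals the planned effect; the upper is not a figure in the article.

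**The case against.** The strongest reply is that the MMRM is neither unusable nor a mere copy of the ANCOVA. This is right in part. The model can be fitted, and with baseline as a response its interaction is the treatment difference in change. A reader might infer that it always uses the same patients and gives the same answer, but the article does not support that. It describes a model in time and treatment with an interaction and states no common baseline mean. In the separate-means form the estimate differs from ANCOVA, and dropouts' baseline values enter the likelihood.

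The equivalence also assumes that the baseline-adjusted means adjust for baseline RHI, which the list of covariates does not name. If they do not, the separate-means MMRM differs from the completers' raw difference in change by (β − 1) × (d in all patients − d in completers). That is a genuine correction for missingness, but small: mean 0.012, maximum 0.025 in the simulations. It still assumes missing at random.

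A reader might also infer that BP, HR and BW, which have repeated visits, are denied an MMRM. That is not established: secondary endpoints are to be analysed in the same way as the primary, and the first MMRM sentence does not name RHI.

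Finally, a separate statistical analysis plan is to be developed and is not shown, so it may contain further checks. Even so, the article fixes MMRM for this purpose, and a plan that follows it inherits the weakness. Fig. 1 is not shown either, but two text sections agree on the RH-PAT schedule.

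**Conclusion.** The point holds in limited form. With a single post-baseline RHI, the MMRM has no intermediate outcome from dropouts and does not vary the missing-at-random assumption. Neither agreement nor disagreement with the primary analysis says much about robustness to the expected 10% dropout. Agreement is automatic if baseline RHI is a covariate, or a response with a common mean, and the ANCOVA adjusts for it. Otherwise the difference mainly reflects how baseline imbalance is handled (0.035 on average and up to 0.084 under the assumed SDs and slope).

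It would go too far to infer that the primary result is biased or the trial's conclusion unsafe. Only a sensitivity analysis is affected; the primary estimate, the type I error rate and the sample size are unchanged. The shift of 0.034 to 0.06 in one arm's mean rests on chosen values and is not a forecast. The plan should be corrected, but this is not a defect that invalidates it.

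**What to change.** In the Statistical analysis plan section, and in the separate plan when written:

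- Drop MMRM as the missing-data check for RHI, and drop or reword the sentence on RHI over time, since the interaction adds no intermediate time point.
- Replace it with multiple imputation of week-24 RHI by arm, from baseline RHI, the four allocation factors and the BP, HR and BW values scheduled at weeks 4 and 12. This still assumes missing at random, but uses post-baseline data that the ANCOVA does not.
- Add a delta-adjusted (tipping-point) or reference-based variant. This is the part that tests the assumption about unobserved values. Fix the range of shifts before unblinding.
- State that the ANCOVA adjusts for baseline RHI as a continuous covariate, if that is intended.
- Keep MMRM for outcomes available at weeks 4, 12 and 24: BP, HR, BW and double product.

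The cost is protocol and plan wording and some programming. No new data are needed, and the article leaves time for it: the analysis plan is to be developed before recruitment ends and the database is locked.

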## Discussion

The EMBLEM trial is an ongoing, prospective, multicenter, placebo-controlled, double-blind, randomized, investigator-initiated clinical trial aiming to assess the effect of empagliflozin on endothelial function in patients with T2DM and established CVD. We hypothesized that empagliflozin can improve endothelial function and thereby ameliorate other vascular markers such as arterial stiffness and sympathetic nervous system (SNS) activity in this patient population (Fig. 2). The primary endpoint is the baseline to 24 weeks change in the RH-PAT-derived RHI, a surrogate marker for endothelial function. In addition, other CV markers, such as arterial stiffness and SNS activity, will be also examined as secondary endpoints as will the potential for a mechanistic association between the changes in such markers by empagliflozin treatment. Thus, this trial has the potential to provide novel clinical evidence on the effect of empagliflozin on vascular function and may help to explain the results of the EMPA-REG OUTCOME trial [10].

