In the present trial, we focused on vascular endothelial function which has a pivotal role in the regulation of vascular tone and circulation which itself is governed by the interplay of vasoconstrictive and vasodilative factors. Endothelial function can be impaired by various metabolic disturbances and is closely associated with increased oxidative stress, inflammation, and insulin resistance [62, 63]. Hence, endothelial dysfunction is paramount to the pathogenesis of atherosclerosis and is considered to be an important marker predictive of the future risk of CV events [64–66]. To make matters worse, evidence has accumulated to suggest that endothelial dysfunction is associated with an increased risk of T2DM through common pathological pathways described previously, synergistically resulting in a higher risk of diabetes-related vascular complications [67–69]. Given these pathophysiological associations, it is imperative to evaluate the therapeutic effect of glucose-lowering agents on endothelial dysfunction in patients with T2DM [30–32, 70]. The existing animal and human data suggest that SGLT2 inhibitors have favorable effects on several biomarkers related to arterial stiffness, myocardial workload, and SNS activity [47, 51, 71, 72], we seek to address whether empagliflozin modulates endothelial function dependently or independently of such markers as secondary endpoints in the trial proposed herein.

The assessment of endothelial function are clinically of importance to obtain the patients’ CV risk or prognosis, and to evaluate the effect of treatment [73, 74]. A number of reports show that T2DM was associated with abnormal endothelial function on the basis of various physiological functional tests, including RH-PAT [75–78]. Moreover, short-term treatment of some DPP-4 inhibitors improved RHI in patients with T2DM [30, 32], in contrast to large-scale outcome trials with DPP-4 inhibitors that failed to demonstrate superior CV safety compared with a placebo [38–40]. Although the reasons for this discrepancy are not yet fully understood, RH-PAT-guided assessments of endothelial function would make a promising tool for the evaluation of drug efficacy. Because treatment with SGLT2 inhibitors can favorably regulate hemodynamic aspects besides those influenced by glucose and lipid metabolism [13–17], it is highly likely that SGLT2 inhibitors impart a more direct and protective effect on the vascular system.

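### The correlations of RHI change with marker changes are planned as plain Pearson coefficients with no arm term; if the arms are pooled, they mix treatment effect with patient-level association and cannot answer the mechanism question.

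*Protocol article*

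**What the plan says.** The Trial endpoints section makes the correlations part of the secondary endpoints: "Secondary endpoints are baseline to 24 week changes in the following parameters and their correlation with the RHI". The Statistical analysis plan section states that "correlations between the changes in the RHI and each measurement listed as a secondary endpoint will be evaluated", and names the statistic: "each measurement listed as a secondary endpoint will be evaluated using Pearson’s correlation coefficient". It gives no arm term, covariate or stratification for these correlations. By contrast, the sentence just before it sends the other secondary comparisons through the same covariance analysis as the primary endpoint.

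The same section fixes the population: "The analyses of the primary and secondary endpoints will be performed in the full analysis set". That set contains both arms. It also sets one threshold for all p values: "p values <0.05 will be considered statistically significant".

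The Discussion gives the correlations their purpose. It plans to examine "the potential for a mechanistic association between the changes in such markers by empagliflozin treatment", and later states the question directly: "we seek to address whether empagliflozin modulates endothelial function dependently or independently of such markers as secondary endpoints".

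**The concern.** In a randomised trial, two outcomes that both respond to treatment are correlated in the combined sample even if they are unrelated among patients on the same treatment. The two arms form two clusters, and a line drawn through the cluster centres has a slope. A Pearson coefficient over all patients cannot separate that slope from an association between individual patients.

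The document expects the conditions for this. Sample size estimation assumes that RHI rises more on empagliflozin than on placebo, and the Discussion describes the drug class as lowering blood pressure and body weight. The artefact would therefore appear when the trial's own hypothesis is true. The stake is the stated mechanistic aim: a marker could be reported as linked to the RHI response only because the drug moved both. The primary comparison is not affected.

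**Working it through.** **Inputs from the protocol article**
- Expected RHI change: 0.40 (empagliflozin) and 0.06 (placebo), difference 0.34 (Sample size estimation).
- 50 evaluable patients per arm, two-sided alpha 5%, power 80% (same section); allocation 1:1 (Randomization and blinding).
- Significance threshold 0.05, two-sided (Statistical analysis plan).

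**Inputs that are assumed**
- SD of RHI change. The article prints the difference as 0.34 ± 0.06 without saying what 0.06 is.
- Size of the drug's shift in a marker, in units of that marker's within-arm SD. The article gives none, so 0.5 to 2.0 is used.
- Changes bivariate normal, with zero correlation within each arm.

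**Step 1. Which SD fits the plan's own sample size?** With n per arm = 2(1.96 + 0.842)² × (SD/0.34)²:
- 0.06 read as an SD: n = 1.
- 0.06 read as the standard error of the difference at 50 per arm: SD = 0.06/√(2/50) = 0.30, so n = 13.
- SD 0.60: n = 48.9, so 49 (50 with the t distribution).

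Solving for the SD at n = 50 gives 0.34 × √25 / 2.802 = 0.607. The stated 50 per arm is reproduced only with an SD of about 0.60, so 0.60 is the central assumption. The values 0.50 and 0.72 serve as a range; 0.72 is the follow-up SD of RHI in the study the article cites.

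**Step 2. Size of the spurious coefficient.** Let d1 and d2 be the arm differences in RHI change and marker change, each divided by its within-arm SD. With equal arms, the pooled covariance is the within-arm covariance plus d1·d2/4, and each pooled variance is 1 + d²/4. With zero within-arm covariance:

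r = (d1·d2/4) / √[(1 + d1²/4)(1 + d2²/4)]

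Here d1 = 0.34/0.60 = 0.567, so 1 + d1²/4 = 1.080. For d2 = 1: r = 0.142/√(1.080 × 1.25) = 0.122. If the drug lowers the marker, r has the same size with a negative sign.

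**Step 3. How often is it declared significant?** At N = 100 the critical |r| is 0.197. Simulation of 20,000 trials per row, 50 per arm:

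| Marker shift (SD) | Spurious r | Pooled Pearson, p < 0.05 | Adjusted for arm, p < 0.05 |
|---|---|---|---|
| 0.5 | 0.07 | 10% | 5% |
| 1.0 | 0.12 | 23% | 5% |
| 1.5 | 0.16 | 38% | 5% |
| 2.0 | 0.19 | 49% | 5% |

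**Step 4. Range over the assumed SD.** For the same four marker shifts, the pooled rejection rate is about 12%, 30%, 50% and 65% at SD 0.50 (d1 = 0.68). At SD 0.72 (d1 = 0.47) it is about 8 to 9%, 17%, 28% and 37%. The arm-adjusted rate stays at about 5% throughout.

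**Step 5. Boundary case.** With d1 = 0 the formula gives r = 0, and the simulated rejection rate is about 5% for every marker shift. The artefact needs a drug effect on both variables.

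**The case against.** The strongest reply is that the text never says the arms are pooled. Within-arm Pearson coefficients would fit the wording, and naming the full analysis set fixes who is included, not whether results are split by arm. The article also announces a statistical analysis plan, not shown here, where such detail could be settled. This stands in part. Pooling is an inference, though the natural one: the statistic is named without mention of arm, in a set of both arms. The point is more than missing detail, because the article fixes a statistic and, on that reading, the statistic does not suit the stated question.

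A reader might infer that every marker the drug moves will appear linked to RHI. The figures do not support that. The artefact also requires an effect on RHI, and at the central SD the spurious r is below the critical value. For shifts of 0.5 to 1.0 SD, most trials (about 77 to 90%) would show no significant link, and even at 2.0 SD slightly more than half would not.

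A reader might also infer that the plan will announce false mechanisms. The Discussion speaks of potential associations and possible mechanisms, and nowhere says that a significant coefficient will be taken as proof. A pooled correlation is a real feature of the combined sample; the error would lie in reading it as a patient-level link.

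Two neighbouring matters carry less weight. Pearson is sensitive to outliers, and several listed biomarkers may be skewed, but the article does not give the distribution of their changes. Many correlations tested at 0.05 will yield some chance findings whether or not arm is handled. Neither is needed for the point about arm.

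**Conclusion.** The concern holds in a conditional form. As written, the correlation analysis does not separate the treatment effect from patient-level association. If the arms are pooled and the drug shifts both RHI and the marker, the coefficient cannot address whether the RHI effect is dependent on or independent of that marker. On the central assumptions the bias in r is small, but the 5% error rate becomes 10 to 49%; across RHI-change SDs of 0.50 to 0.72 the span is roughly 8 to 65%. The upper figures depend on marker shifts of 1.5 to 2.0 SD, for which the document gives no basis. The matter concerns a stated secondary aim and should be corrected before unblinding.

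**What to change.** In the Statistical analysis plan section, and in the later analysis plan, replace the plain Pearson correlation with a partial correlation adjusted for treatment arm, or with a regression of RHI change on marker change that includes arm. Show the within-arm coefficients alongside. Use rank correlation or a log scale where the changes are skewed. Report estimates with 95% CIs, labelled exploratory.

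The cost is a few lines of wording and slightly more analysis work. Coefficients will tend to be smaller where the between-arm difference had been adding to them.

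Adjustment removes the between-arm artefact only. An association within arms between two changes measured after randomisation is still observational and does not by itself establish mediation; the text should say so.
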